## Abstract

**Background:**

Attention Deficit/Hyperactivity Disorder (ADHD) is a neurodevelopmental disorder characterized by difficulties in attention, hyperactivity, and impulse control. Previous studies have suggested that engaging in moderate to vigorous physical activity (PA) and undergoing psychological therapy can help improve ADHD symptoms when combined with pharmacological treatments. This study aims to investigate the effects of parent participation in physical activities and psychological skills training (PST) on the cognitive, emotional, and behavioral outcomes of children with ADHD, as well as the emotional well-being of their parents.

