**Discussion:**

This study’s findings underscore the benefits of greater active participation when children participate in activities with their parents. It will also demonstrate the possible advantages of integrating PA with PST. The research will also explore how these interventions may influence parents, providing insights into whether their engagement enhances their psychological well-being.

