The mental health of parents greatly influences not just their well-being but also their parenting practices as well as the development and mental well-being of their children [19,20]. Parents of children with ADHD experience more parenting stress than parents of children without clinical diagnoses. Additionally, the severity of ADHD symptoms correlates with increased parenting stress, creating a vicious cycle between the two [21,22]. This indicates that interventions should focus on both the children and their parents when addressing ADHD. Moreover, the impact of the interventions may be more significant when both the child and the parents participate in treatments [23]. Parents raising children with disabilities often encounter various challenges that hinder their ability to engage in independent activities away from their children, resulting in difficulties in consistently participating in intervention programs [24,25].

Considering this context, the goal of this study is to explore the impact of PA and PST carried out in tandem by children with ADHD and their primary caregivers. We will assess the effects on the children’s cognitive abilities, emotional states, and behavior. Furthermore, we will investigate how these interventions affect the caregivers’ emotional well-being and anxiety levels. By involving children and their caregivers in these interventions, this study seeks to improve the children’s engagement in PA and PST while providing support to the caregivers to enhance the overall outcomes.

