## Materials and methods

### Study design

This prospective randomized controlled intervention received approval from the Institutional Review Board of Incheon St. Mary’s Hospital (OC24FISI0032) on April 22, 2024. The protocol complies with the Helsinki Declaration and Good Clinical Practice guidelines. Participants will be divided into three groups: intervention group 1 (PA and PST), intervention group 2 (PA), and a control group (no intervention).

Initially, the two intervention groups will be categorized by age. We will randomly assign 18 children and their parents to each group, resulting in 72 participants, using a random number generator (version 1.1). The control group will consist of 18 children and their parents (36 participants) selected from those unable to participate in the interventions but who could complete the assessments. Therefore, the total number of participants across all groups will be 54 children, 54 parents, and 108 individuals.

To enhance the robustness of the analysis and mitigate potential biases from participant dropout, an intention-to-treat (ITT) approach will be implemented. All randomized participants will be analyzed regardless of intervention adherence. Missing data will be managed using multiple imputation methods to preserve data integrity and minimize bias. Additionally, sensitivity analyses will be conducted to evaluate the potential impact of missing data on the study outcomes.

All participants in this study will continue to receive their existing medication treatments throughout the intervention period. Before proceeding with the assessments and interventions, the children and their parents will provide written informed consent. Recruitment and data collection began on May 31, 2024 and is expected to end on February 28, 2025. Data collection and results are expected to be completed by September 30, 2025. Details of the research procedure are presented in Fig 1.

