### Intervention

In this study, intervention group 1 will receive PA and PST, while intervention group 2 will only receive PA. Both groups will engage in the intervention program alongside their primary caregiver. The control group will not receive any intervention. Throughout this process, the child will continue with their existing treatment, and if applicable, the additional intervention will be implemented.

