### Physical activity (PA)

The PA intervention program is based on the meta-analysis conducted by Kim et al. (2022) [6]. On the effects of PA in children and adolescents with ADHD. Specifically, we used the PA program (aerobic exercise and manipulative exercises) from the parent-involved intervention study by Kim et al. (2024) [23,33]. The PA program will be conducted over eight weeks, consisting of two weekly sessions. Each session will last for 90 minutes and include 30 minutes of manipulative exercises followed by 60 minutes of aerobic exercise. The intensity of the PA will be maintained at a moderate to vigorous level, as indicated by a modified Borg Scale rating of 5–7. The level of physical activity will be monitored using the ActiGraph wCT3x-BT (ActiGraph, Pensacola, FL, USA), and efforts will be made to maintain the intensity of moderate to vigorous activity. All sessions will occur in a group setting, with primary caregivers and parents participating. Detailed information about the PA program can be found in Table 1.

**Table 1 pone.0325669.t001:** Physical activity program.

Week	Type	Program Contents
1	manipulative	Rolling and receiving a ball, pushing and stopping a ball with the foot (1m), bouncing a ball in place, and throwing and receiving a ball (1m)
	Aerobic	Horse running, jumping with both feet, step exercises, 10 m shuttle run (10 repetitions) 2 sessions
2	manipulative	Rolling and receiving a ball, pushing and stopping a ball with the foot (2m), bouncing a ball while walking, and throwing and receiving a ball (1m)
	Aerobic	Alternating jumps, jumping with both feet, step exercises, 10 m shuttle run (11 repetitions), 2 sessions.
3	manipulative	Rolling and receiving a ball, pushing and stopping a ball with the foot (3m), bouncing a ball while walking (zigzag), throwing and receiving (1.5m)
	Aerobic	Horse running, jumping with both feet, step exercises, climbing, 10 m shuttle run (12 repetitions) 2 sessions
4	manipulative	Rolling a ball while moving and receiving, pushing a ball while driving and stopping, bouncing a ball while running, and throwing and receiving (2m)
	Aerobic	Alternating jumps, jumping with both feet, step exercises, and a 10 m shuttle run (13 repetitions) for 2 sessions.
5	manipulative	Rolling a ball while moving and receiving, pushing a ball while driving and stopping, bouncing a ball while crossing a balance beam, and throwing and receiving a ball.

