### Psychological Skills Training (PST)

A PST program specifically designed for children with ADHD will be implemented, grounded in essential principles and evidence-based practices of PST. This program will incorporate routines, goal setting, positive self-affirmation, concentration training, and anxiety management techniques (see Table 2). The training aims to enhance attention and alleviate stress and anxiety, which are frequently linked to ADHD. Sessions will be conducted once a week for 50 minutes over 8 weeks, with both primary caregivers and their children participating together in the PST.

**Table 2 pone.0325669.t002:** The Psychological Skills Training Program.

Session (Week)	Program
1	About ADHD
2	The Importance of physical activity
3	Routines Setting
4	Goal Setting
5	Anxiety Control Training
6	Positive Self-Suggestion
7	Attention Focus Training
8	Review of Sessions 2–7

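### For child outcomes, the abstract's aim and conclusion about parent participation cannot be supported, because no arm varies parent participation with the child's activity held fixed

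*Protocol article*

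**What the plan says.** The abstract's Background begins the aim with "This study aims to investigate the effects of parent participation in physical activities and psychological skills training (PST", and names children's cognitive, emotional and behavioural outcomes and parents' emotional well-being as what is affected. The abstract's Discussion then says that the "findings underscore the benefits of greater active participation when children participate in activities with their parents".

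The last paragraph of the Introduction words the goal differently. The study is to "explore the impact of PA and PST carried out in tandem by children with ADHD and their primary caregivers".

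Study design lists the arms as "intervention group 1 (PA and PST), intervention group 2 (PA), and a control group (no intervention"). On who attends:

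- Intervention: "Both groups will engage in the intervention program alongside their primary caregiver", and "The control group will not receive any intervention".
- Physical activity: "All sessions will occur in a group setting, with primary caregivers and parents participating".
- Psychological Skills Training: weekly sessions, "with both primary caregivers and their children participating together in the PST".

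The selection criteria exclude children whose primary caregiver cannot take part. Study design adds that 18 families are randomised to each intervention group, while the 18 control families are selected from those who cannot attend the interventions but can complete the assessments.

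**The concern.** A claim that children benefit from taking part with their parents is comparative: it sets taking part with a parent against taking part without one. To estimate that for the child, some children must do the same programme without the caregiver. The article describes no such group.

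At stake is the headline message. If the intervention arms do better than control, the abstract's wording would let readers credit the trial with evidence for parental involvement. The data would be equally compatible with the whole benefit coming from the child's own exercise or training. The article's case for joint participation, in the Introduction and the body Discussion, rests on earlier work, including a study that compared parent and peer participation groups. This trial does not repeat that comparison.

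**Working it through.** The article gives no figure for this point, so the check is whether the arms allow the effect to be estimated at all.

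**Step 1. What each arm contains** (Study design, Intervention, and the PA and PST sections; 1 = present, 0 = absent)

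| Arm | Child does PA | Caregiver in PA | Child does PST | Caregiver in PST |
|---|---|---|---|---|
| Intervention group 1 (IG1) | 1 | 1 | 1 | 1 |
| Intervention group 2 (IG2) | 1 | 1 | 0 | 0 |
| Control | 0 | 0 | 0 | 0 |

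The two PA columns are identical, and so are the two PST columns. In every arm, the caregiver is present exactly when the child's activity is.

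**Step 2. What can be estimated.** Write the expected child outcome in an arm as

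mean = b0 + a·(child PA) + p·(caregiver in PA) + s·(child PST) + q·(caregiver in PST).

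The three arm means are then:

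- Control: b0
- IG2: b0 + a + p
- IG1: b0 + a + p + s + q

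The three pairwise differences are:

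- IG1 − IG2 = s + q: adding jointly attended PST, with the caregiver present in both arms.
- IG2 − control = a + p: joint PA against nothing.
- IG1 − control = a + p + s + q: joint PA and PST against nothing.

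There are five unknowns and three arm means. Only the sums a + p and s + q can be recovered. Parent participation is p and q, and neither appears apart from the child's activity in any of the three differences. More families would make the sums more precise without separating their parts.

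**Step 3. What each difference rests on.** IG1 versus IG2 is the randomised contrast, with 18 + 18 = 36 families. It estimates joint PST as delivered, including one extra 50-minute session a week for 8 weeks (8 × 50 = 400 minutes of added contact). The two differences against control also carry group contact and the way control families were selected.

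**Step 4. Caregiver outcomes.** Parents have their own measures (parenting stress, anxiety, depression, sleep and physical activity). For these, taking part is the caregiver's own exposure, and it does differ between intervention and control. It never differs without the child's programme differing too. The comparison therefore addresses the joint package for caregivers, against a control group that was not randomised.

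**Step 5. The two aims side by side.** The Introduction's goal, PA and PST carried out jointly, corresponds to a + p and s + q, which the arms address. The abstract's aim, read as written, asks for p and q, which they do not.

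**The case against.** The strongest reply is that the abstract's aim is shorthand. The Introduction and the body Discussion both describe the study as one of PA and PST for children and caregivers, caregiver attendance is a feature of delivery, and the case for joint delivery is drawn from earlier studies. On that reading, parent participation names the package. This stands as far as it goes: the body of the article has an aim that fits the design. It does not rescue the abstract's Discussion sentence, whose subject is the benefit of taking part with parents.

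A second reply is that the present tense of that sentence may be a slip, since the sentences around it are in the future tense and Study design expects results only by September 30, 2025. That is plausible, and a reader should not infer that a result was fixed before the data. Changing the tense alone would still leave a claim that the arms cannot test in children.

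Third, an article condenses a fuller protocol. The point does not depend on anything left out. It rests on the stated aim, the stated conclusion and the stated arms, and no further analysis detail could supply the missing comparator.

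Two stronger readings are tempting and should be resisted:

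- A reader might infer that caregiver participation never varies for any outcome. For caregivers' own outcomes it does vary against control, though bundled with the child's programme.
- A reader might infer that the question the trial can answer is hidden. It is not: the abstract's Discussion names the possible advantage of combining PA with PST, and the arms are built around that contrast.

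**Conclusion.** The two abstract sentences are wrong as written for child outcomes. None of the three pairwise contrasts isolates parent participation, so its effect cannot be estimated whatever the data show and however many families are enrolled. The trial can estimate the effect of adding joint PST to joint PA (randomised, 36 families) and, in a non-randomised comparison, the effect of the joint package against no intervention. For caregiver outcomes, the comparison with control speaks only to the whole package.

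This rests on the arms being delivered as described, with the caregiver attending in both intervention groups.

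It does not follow that the design is unfit for the Introduction's aim, and the documents do not support that wider reading. How the control group is selected is a separate matter; here it only limits what the control comparisons can carry. The correction is one of wording, but it is more than clerical, because it removes a headline conclusion that the design cannot support.

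**What to change.** 1. **Abstract, Background.** Bring the aim into line with the Introduction. For example: to estimate the effect of adding joint PST to joint parent–child PA (intervention group 1 versus 2, randomised), and of the jointly delivered package versus no intervention (non-randomised comparison), on child and caregiver outcomes.
2. **Abstract, Discussion.** Delete the sentence on the benefit of taking part with parents, or recast it prospectively as the effect of the joint package. It should make no claim that taking part with parents is better than taking part without them.
3. **Body Discussion, limitations.** Add to the two limitations listed there (single region, small groups) that there is no child-only arm, so the contribution of parent participation cannot be separated from the child's own programme.

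The cost is a few sentences. If the registry entry repeats the abstract's aim, the same change is needed there. Arms, allocation, assessments, sample size and analysis stay as they are. Keeping parent participation as an aim for child outcomes would instead require a child-only arm, which would be a different trial.

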**Methods:**

Participants for the study will be recruited from a tertiary medical institution. The focus will be on children aged 6–12 years who have been diagnosed with ADHD and are currently receiving treatment at the hospital. Assessments will be conducted separately for the children and their parents. We will evaluate the children’s cognitive, emotional, and behavioral aspects, while for the parents, we will assess only emotional and behavioral aspects.

The study will consist of three Intervention Groups (IG 1 and IG 2) and one control group. IG 1 will receive a combined intervention of PA and PST, IG 2 will participate in PA alone, and the control group will not receive any intervention.

**Discussion:**

This study’s findings underscore the benefits of greater active participation when children participate in activities with their parents. It will also demonstrate the possible advantages of integrating PA with PST. The research will also explore how these interventions may influence parents, providing insights into whether their engagement enhances their psychological well-being.

**Trial registration:**

This study is registered at Clinical Research Information Service (CRIS, https://cris.nih.go.kr) as KCT0010046

## Introduction

Attention Deficit/Hyperactivity Disorder (ADHD) is a neurodevelopmental disorder characterized by a short attention span, inattention, hyperactivity, and difficulties with impulse control [1]. Pharmacotherapy has shown effective results in the short term and is primarily recommended as the first-line treatment option [2]. Most guidelines recommend prioritizing psychoeducation and behavioral management as the first treatment options unless symptoms and impairments are especially severe. There is a general agreement that behavioral management, mainly through parent training, is preferred for children under six [2,3].

Previous studies have investigated interventions incorporating physical activity (PA), medication, and behavioral management [4,5]. These studies have shown that moderate to vigorous PA significantly enhances the neurophysiological, cognitive, emotional, and behavioral aspects of adolescents with ADHD while improving attention, cognitive and executive function, and motor skills [5–7]. Additionally, PA decreases symptoms of depression and anxiety, enabling individuals to manage stress more effectively [8,9]. PA can enhance biological brain health by improving several neurotransmitter systems connected to the hippocampus, upregulating brain-derived neurotrophic factor, and promoting neurogenesis [10,11]. Releasing dopamine, serotonin, and norepinephrine neurotransmitters can enhance attention and memory [12,13].

Psychological skills training (PST) is a technique aimed at developing the ability to manage one’s psychological state positively. This type of training is beneficial not only for athletes but also for individuals in various performance-based fields, such as doctors, soldiers, and performing artists. It helps them achieve peak performance [14–16]. The training includes goal setting, establishing routines, visualization techniques, concentration exercises, anxiety management, mindfulness practices, and positive self-affirmation. When applied to children with ADHD and their parents, this training has demonstrated a decrease in parenting stress and anxiety while also effectively enhancing cognitive, emotional, and behavioral aspects like self-confidence and attention [14,17,18]. Previous studies have indicated that intervention programs for children with ADHD and their parents may contribute to positive enhancements in their emotional and behavioral functioning.

The mental health of parents greatly influences not just their well-being but also their parenting practices as well as the development and mental well-being of their children [19,20]. Parents of children with ADHD experience more parenting stress than parents of children without clinical diagnoses. Additionally, the severity of ADHD symptoms correlates with increased parenting stress, creating a vicious cycle between the two [21,22]. This indicates that interventions should focus on both the children and their parents when addressing ADHD. Moreover, the impact of the interventions may be more significant when both the child and the parents participate in treatments [23]. Parents raising children with disabilities often encounter various challenges that hinder their ability to engage in independent activities away from their children, resulting in difficulties in consistently participating in intervention programs [24,25].

Considering this context, the goal of this study is to explore the impact of PA and PST carried out in tandem by children with ADHD and their primary caregivers. We will assess the effects on the children’s cognitive abilities, emotional states, and behavior. Furthermore, we will investigate how these interventions affect the caregivers’ emotional well-being and anxiety levels. By involving children and their caregivers in these interventions, this study seeks to improve the children’s engagement in PA and PST while providing support to the caregivers to enhance the overall outcomes.

## Materials and methods

### Study design

This prospective randomized controlled intervention received approval from the Institutional Review Board of Incheon St. Mary’s Hospital (OC24FISI0032) on April 22, 2024. The protocol complies with the Helsinki Declaration and Good Clinical Practice guidelines. Participants will be divided into three groups: intervention group 1 (PA and PST), intervention group 2 (PA), and a control group (no intervention).

Initially, the two intervention groups will be categorized by age. We will randomly assign 18 children and their parents to each group, resulting in 72 participants, using a random number generator (version 1.1). The control group will consist of 18 children and their parents (36 participants) selected from those unable to participate in the interventions but who could complete the assessments. Therefore, the total number of participants across all groups will be 54 children, 54 parents, and 108 individuals.

To enhance the robustness of the analysis and mitigate potential biases from participant dropout, an intention-to-treat (ITT) approach will be implemented. All randomized participants will be analyzed regardless of intervention adherence. Missing data will be managed using multiple imputation methods to preserve data integrity and minimize bias. Additionally, sensitivity analyses will be conducted to evaluate the potential impact of missing data on the study outcomes.

All participants in this study will continue to receive their existing medication treatments throughout the intervention period. Before proceeding with the assessments and interventions, the children and their parents will provide written informed consent. Recruitment and data collection began on May 31, 2024 and is expected to end on February 28, 2025. Data collection and results are expected to be completed by September 30, 2025. Details of the research procedure are presented in Fig 1.

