### Participants

#### Selection criteria and recruitment.

Participants for this study will be recruited using purposive sampling, a type of non-probability sampling. Eligible participants will be children diagnosed with ADHD by pediatric psychiatrists at local child and adolescent psychiatry clinics and regional tertiary hospitals where the intervention is conducted. Recruitment announcements will be displayed on hospital screen bulletin boards and within the local community. The inclusion criteria for this study are as follows: 1) Children aged 6–12 years who have received a formal diagnosis of ADHD and are currently undergoing treatment; 2) Children for whom previous Wechsler test results confirm the absence of cognitive decline; 3) Children and parents where the primary caregiver is available to participate in the assessment and intervention. The exclusion criteria for this study include: 1) Children with significant cognitive decline; 2) Children with mental, physical, or medical conditions that would impede participation in PA or PST; 3) Children with any co-occurring disabilities other than ADHD; 4) Children whose primary caregiver is unable to participate; 5) Children involved in other research studies or exercise programs; 6) Children who struggle to cooperate with assessments and interventions. Among children diagnosed with ADHD receiving treatment, those who meet the inclusion/exclusion criteria and desire to participate will be selected.

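### Only the two intervention groups are randomised; the control is selected from families who cannot take part, contrary to inclusion criterion 3, so comparisons with control are open to selection bias that the plan does not acknowledge

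*Protocol article*

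**What the plan says.** All references are to the protocol article.

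- **Label.** Study design opens: "This prospective randomized controlled intervention received approval". It names three groups: physical activity plus psychological skills training (IG1), physical activity alone (IG2), and no intervention.
- **Who is randomised.** The same section says: "We will randomly assign 18 children and their parents to each group, resulting in 72 participants, using a random number generator". The sentence before it concerns the two intervention groups.
- **How control is formed.** The 18 control children and their parents are "selected from those unable to participate in the interventions but who could complete the assessments".
- **Intention-to-treat.** "All randomized participants will be analyzed regardless of intervention adherence".
- **Eligibility.** Selection criteria and recruitment gives one set of criteria for everyone. Inclusion 3 reads "Children and parents where the primary caregiver is available to participate in the assessment and intervention". Exclusion 4 reads "Children whose primary caregiver is unable to participate". Exclusion 2 reads "Children with mental, physical, or medical conditions that would impede participation in PA or PST".
- **Analysis.** Outcome measures puts 54 children in the final analysis, 18 in each of three groups. Statistical analysis plans a repeated-measures ANOVA with time, group and interaction effects, followed by post-hoc t-tests if the interaction is significant. If normality fails, it plans Kruskal-Wallis tests at each time point. No covariate or matching is named.
- **Limitations.** The Discussion lists two: a single region and small groups.

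**The concern.** Inability to take part is the rule that defines the control group, and it is plausibly related to the outcomes. The Introduction itself says that parents of children with disabilities have trouble attending programmes consistently, and that more severe ADHD goes with more parenting stress. Symptom severity (SNAP) and parenting stress (PSI-SF) are both outcomes in Table 3.

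Any claim that physical activity, with or without skills training, does better than no intervention rests on this control. Randomisation protects only IG1 versus IG2, which is the added effect of skills training. A reader who sees a randomised controlled trial with three groups and an intention-to-treat analysis would credit the control comparisons with a protection they lack, and nothing in the article warns against this.

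**Working it through.** **1. Headcount.** Randomised: 2 groups × 18 families × 2 people = 72, the figure stated. Control: 18 × 2 = 36. Total: 72 + 36 = 108, as stated. So 36 of 54 children are randomised, and one third of the study is not. An intention-to-treat set of randomised participants holds 36 children; the planned analysis holds 54.

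**2. Eligibility against the control rule.**
- Inclusion 3 requires availability for the assessment *and* the intervention. The control rule requires assessment without intervention. These conflict directly.
- Exclusion 4 conflicts where the caregiver is the reason for not attending.
- Exclusion 2 applies where a condition of the child is the reason.
- No separate criteria for controls are given.

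**3. Correlation used below.** The article states no correlation between visits. Its pre-dropout sample size of 45 is reproduced with ρ = 0.5: λ = f²·N·m/(1−ρ) = 0.0625 × 45 × 3 / 0.5 = 16.875, with df 4 and 84, α = 0.0167 and power 0.81. I therefore assume ρ = 0.5.

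**4. Illustration: constant shift.** Assumptions, none from the documents: no treatment effect, control shifted by d SD at all three visits, 18 per group, α = 0.05.

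*Group main effect.* The mean of three visits has variance (1 + 2 × 0.5)/3 = 2/3. With one of three groups shifted, the squared deviations of the group means sum to (2/3)d². So λ = 18 × (2/3)d² / (2/3) = 18d², with df 2 and 51.

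| Planned test | d = 0.3 | d = 0.5 | d = 0.8 |
|---|---|---|---|
| λ, group main effect | 1.62 | 4.50 | 11.52 |
| Group main effect rejects | 18% | 44% | 85% |
| Kruskal-Wallis at a follow-up visit (simulated) | 13% | 29% | 64% |
| Group-by-time interaction (simulated) | about 5% | about 5% | about 5% |
| IG1 vs control t-test at visit 2, only after a significant interaction (simulated) | 1% | 2% | 3% |

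Simulation of the main effect gives 18%, 45% and 84%, the same within simulation error.

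**5. Illustration: different time course.** Suppose instead that control starts level but differs by d SD at both follow-up visits for reasons unrelated to treatment. The time deviations (−2/3, 1/3, 1/3)d have squares summing to (2/3)d², and the same factor 2/3 applies for groups. So λ = 18 × (2/3) × (2/3)d² / (1 − 0.5) = 16d², with df 4 and 102. The values 1.44, 4.00 and 10.24 give rejection in 13%, 31% and 70% of trials. The interaction is not safe here.

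**6. Does baseline adjustment cure it?** Under the constant shift with ρ = 0.5, adjusting for baseline removes about ρ × d, half the shift. Analysis of covariance, IG1 versus control, still rejects in about 8%, 13% and 23–24% of trials. Change scores stay near 5%. Under other selection mechanisms the ranking can differ.

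**The case against.** The strongest reply is that the study is sized on the group-by-time interaction, which cancels a constant difference between groups, and that between-group t-tests follow only if the interaction is significant. This stands. Without that condition, the t-test at one follow-up visit would reject in about 14%, 32% and 64% of trials for the three shifts. A reader might take those as error rates of the plan, but they do not describe the procedure as written, which gives 1–3%. The reply does not cover the group main effect or the Kruskal-Wallis tests, which are planned without that condition, nor a control group with a different course.

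Four stronger readings are tempting and not supported:

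- **That controls are hand-picked.** The text says they are selected and gives no mechanism.
- **That intention-to-treat is claimed for all three groups.** It is stated for randomised participants only. The fault is the mismatch with a 54-child analysis.
- **That every control comparison is biased.** The documents support a risk; neither its size nor its direction can be derived.
- **That every control family breaches exclusion 4.** That criterion does not say what the caregiver cannot participate in, controls do attend assessments, and the reason for non-attendance is not stated. Inclusion 3 is the clear conflict.

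It is also fair to say that choice of covariates may sit in an analysis plan not shown, and that making IG1 versus IG2 the sole confirmatory contrast would be a matter of preference. Neither excuses the label or the conflict between criteria, which the article itself states.

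**Conclusion.** The point holds on the text. The control is not randomised, its selection rule contradicts inclusion criterion 3, the randomised label is too broad, the intention-to-treat set does not match the analysis set, and the limitation is missing. IG1 versus IG2 is unaffected.

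The numerical consequence is conditional. If the control differs by a constant 0.3 to 0.8 SD, the group main effect misleads in roughly 18% to 85% of trials against a nominal 5%, while the interaction and the t-tests conditional on it do not. If the control follows a different course, or regresses to the mean differently, the interaction can mislead too. These shifts, the correlation of 0.5 and the absence of a treatment effect are assumptions.

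**What to change.** 1. Confine the words randomised and intention-to-treat to IG1 versus IG2 (36 families).
2. Describe the control as a concurrent non-randomised comparison group and report IG-versus-control results as such. Do not rest claims of effect against control on the group main effect or on unadjusted single-visit comparisons. Base them on change from baseline (group-by-time), with a baseline- and age-adjusted analysis as sensitivity, and state that neither fully removes selection bias.
3. Give controls their own eligibility criteria, so that inclusion 3 and exclusion 4 no longer conflict with the control selection rule.
4. Add the non-randomised control to the limitations.

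The cost is wording in the protocol and registration, plus one sensitivity analysis on data already planned. Recruitment was due to end on 28 February 2025, so relabelling and re-analysis are more realistic than randomising a new control. The downside is a weaker claim against control.
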